### Outcome measures

The primary endpoint is the proportion of participants with HIV-1 RNA < 50 copies/mL at Week 24 using pure virologic response (PVR).

Pure virologic response is defined as follows:
On study treatmentNo confirmed virologic rebound defined as:
o HIV RNA ≥ 50 copies/mL on 2 consecutive visitso HIV-1 RNA ≥ 50 copies/mL during study followed by premature discontinuationDiscontinuation prior to week 24 for reasons other than virologic rebound (i.e. no data in window and last HIV RNA < 50 copies/mL) are considered PVR

Secondary outcome measures include the following:
Proportion of patients with HIV RNA < 50 copies/mL at week 48 using PVRProportion of patients with HIV-1 RNA < 50 copies/mL at weeks 24 and 48 using PVR in those with any archived resistance detected in proviral DNAEmergence of new resistance mutations in participants with two consecutive viral load ≥50 copies/mL measured 2–3 weeks apartSafety and tolerability of B/F/TAF FDC in participants switching from bPI-based regimens at 48 weeks based on clinical presentation and laboratory resultsChange from baseline in patient reported outcomes at weeks 24 and 48 measured using the *HIV Symptom Distress Module (HIV-SI)* and the *Pittsburgh Sleep Quality Index (PSQI)* questionnaires.Change from baseline in serum lipid concentrations at weeks 24 and 48Change from baseline in HBA1c in blood weeks 24 and 48Change from baseline in weight and BMI at weeks 24 and 48

### Sample size justification

We considered a number of sample size scenarios bearing in mind the pilot nature of the study (Table 1). We will perform a futility analysis at 24 weeks when assessing the primary outcome. At 24 weeks, with 98 participants in the trial, we will have 80% power for 10% significance to conclude non-inferiority of the B/F/TAF arm assuming a non-inferiority margin of 13% and viral suppression in 90% of participants in both arms.

**Table 1 Tab1:** Sample size scenarios

Confidence level	Lower limit of CI	Upper limit of CI	Sample size per arm	Total sample size
95%	80	96%	62	124
90%	80	96%	50	100
80%	80	95%	38	76

For the study to continue beyond 24 weeks, we need 90% (45/50) of the individuals randomised to the B/F/TAF arm to be suppressed with the lower limit of the confidence interval to just lie above 80%. Recruiting 50 participants per arm would achieve this at the 90% confidence level. The sample size required decreases as the level of confidence in our estimates decreases.

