## Methods

### Trial design

The PIBIK trial is a phase IV, investigator-initiated, prospective, multicentre, open label pilot, randomised two arm study to assess the safety and efficacy of switching from a bPI-based regimen to B/F/TAF single tablet regimen in INSTI-naïve, virologically suppressed HIV-1 Infected adults harbouring drug resistance mutations. The allocation ratio is 1:1 (Fig. 1).

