### Recruitment

We have allowed 12 months to recruit 100 participants over the seven sites involved in the trial. This requires recruitment of 1–2 participants per month per site which is deemed feasible. Each site has been allocated a target of 14–15 subjects. In the case of slow enrolment, additional sites will be offered participation in the study.

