### Statistical analysis

All randomised patients who received at least one dose of the study medication will be included in the analysis.

Summary statistics will be presented by trial arm using median with interquartile ranges for continuous variables with skewed distributions or mean with standard deviations for normally distributed variables. Categorical variables will be summarised using frequencies and proportions.

Non-inferiority for the futility analyses will be concluded if the lower bound of a two-sided 90% CI for the difference in proportions (B/F/TAF minus boosted PI) of patients with plasma HIV-1 RNA < 50 copies/mL at week 24 is greater than − 13%.

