#### Primary outcome analyses

##### Primary efficacy endpoint

Proportions of individuals with HIV RNA < 50 copies/mL at 24 weeks will be estimated using PVR.

The percentage of participants with PVR for HIV-1 RNA cut-off at 50 copies/mL at Week 24 will be summarized.

Differences between trial arms will be estimated together with 95% confidence intervals.

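### The stated 80% power with 98 participants does not belong to the stated non-inferiority rule; under the two-sided 90% CI it is about 65–69%

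*Protocol article*

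**What the plan says.** The Sample size justification gives one power statement for week 24: "with 98 participants in the trial, we will have 80% power for 10% significance to conclude non-inferiority of the B/F/TAF arm". The scenario behind it is a 13-point margin with 90% suppression in each arm. The statement does not say whether the 10% is one-sided or two-sided. Trial design states that "The allocation ratio is 1:1", so 98 participants are 49 per arm.

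Statistical analysis gives the decision rule: "Non-inferiority for the futility analyses will be concluded if the lower bound of a two-sided 90% CI for the difference in proportions". That bound must lie above −13 points; the difference is suppression at week 24 in the B/F/TAF arm less that in the comparator arm. No other non-inferiority rule appears in the article.

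Under Primary efficacy endpoint, the same week-24 difference appears again: "Differences between trial arms will be estimated together with 95% confidence intervals". No margin or test is attached to that interval.

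Two further statements bear on the size. Recruitment says "We have allowed 12 months to recruit 100 participants over the seven sites involved in the trial". Table 1 and the text below it justify 50 per arm by single-arm precision: 45 of 50 suppressed on B/F/TAF, with the lower 90% confidence limit just above 80%. The text makes this a condition for continuing beyond week 24.

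**The concern.** A power figure has meaning only for a particular decision rule. The lower bound of a two-sided 90% interval is a one-sided 5% test. If the 80% was calculated for a one-sided 10% test, the article credits its rule with power that the rule does not have.

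What is at stake is how the week-24 result is read. If the arms are truly equal at 90%, the article implies a 20% chance of failing to conclude non-inferiority, whereas the stated rule carries roughly a one-in-three chance. A reader who trusts the 80% would take a failed comparison as stronger evidence against the switch than the design supports.

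**Working it through.** **Inputs, all from the article**
- 98 participants at 1:1, so n = 49 per arm; recruitment target 100, so 50 per arm.
- Suppression 90% in each arm, so the true difference is 0.
- Margin 0.13.
- Target power 80%, z = 0.8416.
- Level: 10%, sidedness not stated. Rule: two-sided 90% CI, one-sided 5%.

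No drop-out inflation is stated, so none is applied.

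**Step 1: reproduce the plan's figure.** With unpooled variance, n per arm = (z_α + 0.8416)² × (2 × 0.9 × 0.1) / 0.13² = (z_α + 0.8416)² × 0.18 / 0.0169.

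| One-sided level | Matching two-sided CI | z_α | n per arm | Total |
|---|---|---|---|---|
| 10% | 80% | 1.2816 | 48.01 → 49 | 98 |
| 5% | 90% | 1.6449 | 65.85 → 66 | 132 |
| 2.5% | 95% | 1.9600 | 83.60 → 84 | 168 |

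The article's 98 appears exactly at one-sided 10% and at neither of the other levels.

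**Step 2: power at the stated size.** Power = Φ(0.13 / SE − z_α), with SE = √(0.18 / n).

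At n = 49, SE = 0.0606 and 0.13 / SE = 2.145:
- one-sided 10%: Φ(2.145 − 1.282) = Φ(0.863) = 80.6%, the article's 80%;
- one-sided 5%, the stated rule: Φ(2.145 − 1.645) = Φ(0.500) = 69.1%.

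At n = 50, SE = 0.0600 and 0.13 / SE = 2.167. Under the stated rule, Φ(2.167 − 1.645) = Φ(0.522) = 69.9%. The planned 100 participants do not close the gap.

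**Step 3: does the interval method matter?** The table gives power at 49 per arm from enumerating all pairs of binomial outcomes with 90% in both arms.

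| Interval | 80% CI (one-sided 10%) | 90% CI (one-sided 5%) |
|---|---|---|
| Wald | 81.1% | 69.2% |
| Agresti–Caffo | 79.6% | 69.2% |
| Newcombe | 79.6% | 64.8% |
| Score (Farrington–Manning) | 79.6% | 64.7% |
| Wald, continuity-corrected | 70.8% | 59.8% |

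No method reaches 80% under the 90% interval. Leaving aside the conservative continuity-corrected version, the range is 65–69%. With 50 per arm, Wald gives 71.2%, and Newcombe and score give 67.1%.

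**Step 4: check the other basis for the size.** For 45 of 50, the exact (Clopper–Pearson) 90% limits are 80.1% and 96.0%. These match the 90% row of Table 1, so that justification stands.

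**The case against.** **The sample size has another basis, and this is a pilot.** This stands. Table 1 supports 50 per arm by single-arm precision, the 45/50 continuation criterion belongs to that argument, and the article promises only preliminary evidence. A reader might infer that the sizing of the trial collapses, and it does not. But the article also makes a numerical power claim for the randomised comparison and sets a formal rule for it, and a pilot with modest power should still state that power correctly.

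**The 90% suppression rate may be pessimistic.** The Background cites 93% suppression on B/F/TAF in another switch study, and pure virologic response counts discontinuations without rebound as successes. If 93% is assumed in both arms, power under the 90% interval at 49 per arm is 81% (normal approximation), 80% (exact Wald) or 74% (Newcombe). At 95% it is 90%, 88% or 83%. So 65–69% is not a forecast of what the trial will achieve. It is, however, the power under the assumptions to which the article attaches its 80%.

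**The rule is described as one for futility.** The Sample size justification places the futility analysis at week 24, when the primary outcome is assessed, and its power sentence is about concluding non-inferiority. This is the only rule that the sentence can refer to.

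**Stronger readings that the article does not support.**
- A reader might infer that the true power is about 57%, since Φ(2.145 − 1.960) = 57.3% on a 95% interval. The article gives that interval for estimation and never ties it to the margin, so 57% is the power of a rule the protocol does not specify.
- A reader might infer that two interval levels leave the conclusion open to choice after the data are seen. The level, bound and margin of the deciding interval are all fixed under Statistical analysis.
- A reader might infer that every randomised comparison is affected. Safety endpoints also plans between-arm comparisons of lipids, HbA1c, weight, BMI and patient-reported outcomes; the power sentence does not concern them.
- A reader might infer a loosened error rate. The stated rule is stricter than the level that reproduces the power figure.

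**Conclusion.** The power statement is wrong as written. Under the article's own assumptions (90% in both arms, 13-point margin, 49 per arm) and its own rule (two-sided 90% interval), power is about 69%, or about 65% with a Newcombe or score interval, against a stated 80%. The chance of missing non-inferiority when the arms are equal is therefore about 31–35%, not 20%. Reaching 80% under that rule would take about 132 participants by the normal approximation.

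The likely cause is that 10% was used as a one-sided level in the calculation and read as two-sided in the analysis section. The exact match at 98 suggests this, but because the text does not give sidedness it remains an inference. The mismatch does not depend on it: 98 does not give 80% power under the stated rule at the stated rates.

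The error is confined to the stated power of the week-24 non-inferiority comparison.

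**What to change.** Keep the sample size and the decision rule. Replace the power sentence with one that matches the rule, for example: with 49 participants per arm, 90% suppression in both arms and a 13-point margin, power is about 65–69%, depending on the interval method, when non-inferiority is judged on the lower bound of a two-sided 90% confidence interval. If the interval method is already settled, give the single figure for it.

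As a minor clarification, state that this 90% interval alone decides non-inferiority and that the 95% interval under Primary efficacy endpoint is descriptive.

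This takes one or two sentences and no additional participants. The downside is a stated power that looks less favourable.

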### Recruitment

We have allowed 12 months to recruit 100 participants over the seven sites involved in the trial. This requires recruitment of 1–2 participants per month per site which is deemed feasible. Each site has been allocated a target of 14–15 subjects. In the case of slow enrolment, additional sites will be offered participation in the study.

### Allocation and blinding

The web-based Sealed Envelope™ system will be used to allocate individuals randomly to Arm 1 and Arm 2. The statistician will provide the randomisation list. Each study site will be provided with a randomisation guide. The Sealed Envelope™ system will randomise subjects within 8 strata as shown in Table 2.

**Table 2 Tab2:** Randomisation strata

Stratum	Baseline Protease-inhibitor Regimen	Use of lipid lowering therapy at study day 1	No of baseline mutations of the NRTI class^**a**^
I	Atazanavir	Yes	< 2
II	Atazanavir	Yes	≥2
III	Atazanavir	No	< 2
IV	Atazanavir	No	≥2
V	Darunavir	Yes	< 2
VI	Darunavir	Yes	≥2
VII	Darunavir	No	< 2
VIII	Darunavir	No	≥2

^a^From historical genotype report assessed during screening

The purpose of the stratification is to balance the treatment arms on important prognostic factors such as:
The bPI used in the subject’s baseline regimen (Atazanavir or Darunavir)Use of lipid lowering therapy at study day 1 (yes/no)Number baseline mutations of the NRTI class (< 2 vs. ≥2)

Investigators randomise patients by completing an on-screen form with patient details, stratification factors, inclusion and exclusion criteria. Investigators are immediately shown the treatment allocation. Trial managers have real-time access to recruitment statistics and are notified by email of every new randomisation. The randomisation application conforms to the requirements of FDA 21 CFR part 11, Electronic Records; Electronic Signatures and ICH GCP. No-one can delete records from the randomisation database, so that all randomisations have to be accounted for. Audit log files detailing all activity on the randomisation system are available to the trial manager. Neither the investigators nor the participants will be blinded to the treatment allocation.

### Data collection

The presence of resistance mutations will be determined using historical genotype results obtained in local laboratories in those eligible according to the inclusion and exclusion criteria. We would obtain more information on resistance mutations by sequencing cell-associated HIV-1 DNA in peripheral blood mononuclear cells prior to commencing B/F/TAF. The results of proviral DNA sequence will not be available in real time and will not be used to inform treatment decisions but will further the understanding of the clinical importance of archived resistance mutations, if any, in individuals developing virological failure.

The baseline visit will not exceed 30 days after the screening visit. Follow up of participants will continue until all participants have accrued 48 weeks from their baseline visits. Individuals who have completed Week 48 visit will be followed up 30 days post cessation of trial treatment via a telephone call or a standard of care clinical appointment for performance of the following assessments; adverse events and symptoms review, HIV associated conditions, concomitant medications and for women of child bearing potential (WOCBP), confirmation that contraception has been used in the previous 30 days.

Study procedures, screening, randomisation and safety monitoring will be according to attached visit schedule in Table 3.

**Table 3 Tab3:** Trial procedures and Timelines

Weeks	Screening (− 30 days)	Baseline (FV)	4	12	24 (FV)	28	36	48 (FV)	Early termination visit (FV)	30 day post treatment follow up *(telephone call or standard of care clinic visit)*
**Informed consent**	X									
**Demographic data and medical history including full ART history**	X									
**Eligibility criteria**	X	X								
**Review of historical drug resistance tests**	X									
**Adverse events**		X	X	X	X	X	X	X	X	X
**Concomitant medications**	X	X	X	X	X	X	X	X	X	X
**HIV-SI**		X			X			X	X	
**PSQI**		X			X			X	X	
**HIV associated conditions**	X	X	X	X	X	X	X	X	X	X
**Randomisation**		X								
**e-Case Report Forms**	X	X	X	X	X	X	X	X	X	X
**Vital signs (Blood Pressure, Pulse, temperature, weight)**	X	X	X		X	X		X	X	
**Complete/**^***a***^***symptom directed physical examination***	X	X^a^	X^a^	X^a^	X^a^	X^a^	X^a^	X^a^	X^a^	
**Height**	X									
**Weight, BMI & waist circumference**	X	X	X		X	X		X	X	
**12 Lead ECG**	X				X			X	X	
**Urinalysis**	X	X	X		X	X		X	X	
**Urine Pregnancy Test**	X	X	X		X	X		X	X	
**CD4/CD8 T cell count**		X			X			X	X	
**HIV-1 RNA viral load (& resistance testing if > 50 copies/mL)**	X	X	X	X	X	X	X	X	X	
**Whole blood for Proviral DNA**		X								
**Haematology**	X	X	X		X	X		X	X	
**Urea, electrolytes, creatinine, phosphate, glucose, calcium, amylase**	X	X	X		X	X		X	X	
**Estimated GFR**	X	X	X		X	X		X	X	
**UPCR**	X	X	X		X	X		X	X	
**HBV & HCV serology**	X									
**Liver function tests**	X	X	X		X	X		X	X	
**Lipids (Fasting Cholesterol, LDL, HDL, Triglycerides)**		X			X			X	X	
**HbA1c**		X			X			X	X	
**Pill count adherence**		X	X	X	X	X	X	X	X	
**Self-reported adherence**		X	X	X	X	X	X	X	X	
**Study drug dispensation**		X	X	X	X	X	X			
**Study drug accountability**			X	X	X	X	X	X	X	

*FV* Fasting visit, *HIV-SI* HIV symptom distress module, *PSQI* Pittsburgh Sleep Quality Index, *BMI* Body mass index, *UPCR* urine protein creatinine ratio, *HBV* Hepatitis B virus, *HCV* Hepatitis C virus, *LDL* Low density lipoprotein, *HDL* High density lipoprotein

Individuals with virological failure defined as a rebound in HIV-1 RNA ≥ 50 copies/mL, which is subsequently confirmed at the following scheduled or unscheduled visit. Following the initial detection of virological rebound, subjects will be asked to return to the clinic for a scheduled or unscheduled blood draw (2 to 3 weeks after the date of the first measured rebound) for repeat viral load testing. If virological rebound is confirmed and the HIV-1 RNA is ≥200 copies/mL, the blood sample from the confirmation visit will be the primary sample used for HIV-1 genotypic testing. After a participant’s first post-baseline resistance test, additional testing will be conducted on a case-by-case basis. Any participant may be discontinued at the investigator’s discretion or per local treatment guidelines. If no resistance is detected from the genotype, the participant may remain on study drugs and a repeat HIV-1 RNA measurement should be performed (2 to 3 weeks after date of test with HIV-1 RNA ≥ 50 copies/mL). Investigators should carefully evaluate the benefits and risks of remaining on study drug for each individual participant and document this assessment in the on-site medical record.

Data on patient reported outcome measures will be collected using the HIV-SI and the PSQI. The HIV-SI is a validated, self-administered 20-item health-state questionnaire for use in clinical care and research amongst people living with HIV (PLHIV)in order to identify and address common and bothersome symptoms associated with HIV treatment and disease [16]. The instrument is considered to be the gold standard in contemporary HIV-symptom research [17]. Respondents will be asked about their experience with each 20 symptoms during the past 4 weeks using a 5-point Likert scale. Response options and scores are as follows: 0) I don’t have this symptom, 1) I have this symptom and it doesn’t bother me, 2) I have this symptom and it bothers me a little, 3) I have this symptom and it bothers me, 4) I have this symptom and it bothers me a lot.

The Pittsburgh Sleep Quality Index (PSQI) is a self-rated questionnaire which assesses sleep quality and disturbances over a 30-day recall period [18]. Nineteen individual items generate seven component scores: subjective sleep quality, sleep latency, sleep duration, habitual sleep efficiency, sleep disturbances, use of sleeping medication, and daytime dysfunction. It uses a Likert scale in with the following scores: 0) Not during the past month, 1) less than once a week, 2) once or twice a week, 3) Three or more times a week. The sum of scores for these seven components yields one global score (0 to 21). A total score of 5 or greater is indicative of poor sleep quality.

Participants with early study termination from whatever cause will undergo the assessments outlined in Table 3.

### Data management

A source data worksheet will be created to capture all the relevant information and will be filed as source documentation in the participants’ notes. Questionnaires and self-report VAS scores will also be completed by the patients. A source data agreement will be completed prior to recruitment commencing to ensure all parties are aware which documents constitute source data.

Data from the source will be entered onto the electronic case report form (eCRF) on the web-based MACRO™ electronic data capture system. Data entered will be checked by the Data Manager in accordance with the Data Management Plan (supplementary appendix) and queries raised to the clinical sites via MACRO when appropriate. Clinical sites will be responsible for the entry of data into the eCRF. Patient data will be entered using study number only and no patient identifiable data will be seen by the data management team.

Direct access will be granted to authorised representatives from the sponsor, host institution and the regulatory authorities when appropriate to permit trial-related monitoring, audits and inspections.

Archiving will be the responsibility of the sponsor and all documentation will be archived for 25 years, with the exception of the health records which will be kept in accordance with UK law and local policy. The sponsor named archivist will be responsible for ensuring the documentation is prepared in line with the relevant sponsor standard operating procedures.

### Statistical analysis

All randomised patients who received at least one dose of the study medication will be included in the analysis.

Summary statistics will be presented by trial arm using median with interquartile ranges for continuous variables with skewed distributions or mean with standard deviations for normally distributed variables. Categorical variables will be summarised using frequencies and proportions.

Non-inferiority for the futility analyses will be concluded if the lower bound of a two-sided 90% CI for the difference in proportions (B/F/TAF minus boosted PI) of patients with plasma HIV-1 RNA < 50 copies/mL at week 24 is greater than − 13%.

#### Primary outcome analyses

##### Primary efficacy endpoint

Proportions of individuals with HIV RNA < 50 copies/mL at 24 weeks will be estimated using PVR.

The percentage of participants with PVR for HIV-1 RNA cut-off at 50 copies/mL at Week 24 will be summarized.

Differences between trial arms will be estimated together with 95% confidence intervals.

#### Secondary outcome analysis

##### Secondary efficacy endpoint

Proportions of individuals with HIV RNA < 50 copies/mL at 48 weeks will be estimated using PVR.

The percentage of participants with PVR for HIV-1 RNA cut-off at 50 copies/mL at Week 48 will be summarized.

Differences between trial arms will be estimated, together with 95% confidence intervals. The proportion of patients with HIV-1 RNA < 50 copies/mL at weeks 24 and 48 using PVR in those with any archived resistance detected in proviral DNA will be estimated.

The proportion of patients with any emergent drug resistance following virological rebound will be estimated.

